##### List of clinical data and blood samples to be collected

List of clinical data and blood samples to be collected is shown in Tables 2 and 3.

#### Data management

Study data will be entered in the pseudonymized form in a study database by authorized and trained members of the study team via electronic case report forms (eCRF). The electronic data capture system REDCap^TM^ is used for data acquisition. This system uses built-in security features to prevent unauthorized access to patient data, including an encrypted transport protocol for data transmission from the clinical site to the study database. An audit trail provides a history of the data entered, changed, or deleted, indicating the processor and date. Access will be granted to authorized personnel only, and only if they have received appropriate training. The study database is located on a server of the IT facility (Klinikrechenzentrum, KRZ) of Medical Center - University of Freiburg. This server is expertly protected against access over several levels (see also the documentation of the IT facility).

The decision and control over the use of study data lie with the coordinating investigator. Compliance with relevant data protection regulations according to the EU-GDPR, federal and local data protection laws is guaranteed.

#### Statistical methods

##### Statistical methods for analyzing primary and secondary outcomes

Confirmatory statistical testing will be restricted to the analysis of the primary outcome, to be followed by descriptive reporting of other trial results**.** Emphasis will be given to reporting of effect estimators with two-sided 95% confidence intervals rather than *p* values, which will be considered statistically significant if below 5% for tests of equality.

In the primary analysis, randomized groups will be compared using a sequential closed test procedure: To guarantee a multiple significance level of 5%, confirmatory statistical testing at nominal significance level *α*=5% will continue until the first non-significant result, followed by descriptive reporting of the results of subsequent analyses. Treatment arms will be compared in the following order: CRRT with CytoSorb versus CRRT without CytoSorb, CRRT without CytoSorb versus no CRRT, CRRT with CytoSorb versus no CRRT.

The effects of CRRT with CytoSorb versus CRRT without CytoSorb with respect to the primary endpoint serum bilirubin level after 72 h will be estimated and tested within a linear regression model, and the two-sided 95% confidence interval will be calculated. The model will include randomized treatment group and continuous baseline bilirubin level as independent variables. Robust standard errors will be used to allow for different error variability in the two treatment groups. The two-sided test for a difference between the interventions CRRT with CytoSorb and CRRT without CytoSorb at significance level 5% will be based on the two-sided 95% confidence interval from the linear regression model. This is expected to increase the power compared to a t-test, due to adjustment for baseline bilirubin level. The same modeling approach will be employed for the comparisons of CRRT without CytoSorb versus no CRRT and CRRT with CytoSorb versus no CRRT, respectively.

No interim analysis will be performed for the primary endpoint. Before the end of the study and enrollment of all participants, no early confirmatory conclusion of the superior efficacy of the study intervention can be drawn.

The most relevant secondary endpoint is survival time from baseline since these data are planned to be used for the sample size calculation in a subsequent multi-center trial where survival time will serve as the primary endpoint. Due to the frequent application of cytokine adsorption in medical practice, a subsequent trial will be warranted even if the data of this trial will not show a benefit for cytokine adsorption. The effects of CRRT with CytoSorb versus CRRT without CytoSorb with respect to survival time will be estimated and tested by Cox regression. The regression model will include treatment and continuous baseline bilirubin level as independent variables. As an estimate of the effect size, the hazard ratio between the two treatment arms will be given with the corresponding asymptotic two-sided 95% confidence interval. Rates of patients surviving from baseline will be estimated for the three treatment arms using the Kaplan-Meier method.

Another important secondary aspect of the trial is the preparation of translational research into the mechanism of action induced by cytokine adsorption. To this end, an exploratory analysis of a broad array of clinical and inflammatory parameters with a potential role in ACLF will be performed. Statistical analysis will be designed to identify those parameters that are most clearly affected by cytokine adsorption. The primary focus will be on patients randomized to CRRT with CytoSorb and CRRT without CytoSorb. During initial data analysis, a pre-specified set of monotone transformations will be applied to the 72 h measurements of each parameter in the array, with the aim to reduce skewness. The skewness of the transformed values will be calculated for each parameter and each transformation. Among the transformations considered, the one yielding the mean skewness closest to zero, averaging skewness over parameters, will be selected and applied to both baseline and 72 h measurements of each parameter. For each parameter, the effects of CRRT with CytoSorb versus CRRT without CytoSorb with respect to the change from baseline (transformed value after 72 h minus transformed value at baseline) will be tested within a linear regression model including treatment and the transformed baseline value as independent variables. Robust standard errors will be used to allow for different error variability in the two treatment groups. The two-sided p-values based on these linear regression models will be adjusted for multiple testing using the Benjamini-Hochberg method to control the False Discovery Rate of parameters claimed to differ between treatments at the 5% level [43, 44].

Descriptive analyses of the remaining secondary endpoints will be performed with regression models or statistical tests as appropriate for the respective type of data.

For safety reasons, mortality will be closely monitored throughout the trial. Criteria for early termination of the study are listed and explained in the “Early termination of the study” section.

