#### Sample size

In this study, the randomization to the treatment arms CRRT with CytoSorb, CRRT without CytoSorb, and no CRRT will be done with a 1:1:1 ratio. The group with no CRRT is included merely for exploratory analysis of safety aspects and does not affect the power analysis. The sample size calculation is motivated by data from case reports and retrospective case series, according to which serum bilirubin levels in patients with liver failure could be reduced by 50% by adsorption in the CytoSorb adsorber for 72 h [17–20]. We expect a mean of 10 mg/dl serum bilirubin at baseline, no change in control patients, and a reduction to a mean of 5 mg/dl after 72 h in the cytokine adsorption group. The typical range, 1 to 20 mg/dl, implies an expected standard deviation of about 5 mg/dl. This is a conservative estimate, as the inclusion criterion, bilirubin >5mg/dl, was not considered for the calculation. On the basis of a two-group *t*-test with a two-sided significance level of 5%, a sample size of 17 patients in each group yields a power of 80% to detect a difference if it is assumed that the mean serum bilirubin levels after 72 h differ by 5 mg/dl, given a standard deviation of 5 mg/dl in both groups. This is conservative in that we anticipate a lower standard deviation after 72 h in the intervention group. No missing values up to 72 h are expected. Hence, the numbers of patients to be randomized to the three treatment arms are *n*=17:17:17.

In the unexpected event that patients die within the study before reaching the 72-h end point, we will describe an appropriate expansion of enrolment in an amendment to this study protocol.

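### Minor: the fixed test order makes CRRT versus no CRRT an unnecessary gate before CytoSorb plus CRRT versus no CRRT, and the no-CRRT arm is called exploratory in one section but tested confirmatorily in another

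*Protocol article*

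**What the plan says.** The section Statistical methods for analyzing primary and secondary outcomes confines confirmatory testing to the primary outcome, 72-h serum bilirubin, and sets a sequential closed procedure: "confirmatory statistical testing at nominal significance level *α*=5% will continue until the first non-significant result". Whatever follows the stop is reported descriptively. The order is fixed: "Treatment arms will be compared in the following order: CRRT with CytoSorb versus CRRT without CytoSorb, CRRT without CytoSorb versus no CRRT", and third CRRT with CytoSorb versus no CRRT. All three comparisons use linear regression on treatment and baseline bilirubin with robust standard errors.

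The Sample size section plans on a baseline mean of 10 mg/dl, "no change in control patients", a 72-h mean of 5 mg/dl with CytoSorb, an SD of 5 mg/dl and 17 patients per arm. Of the third arm it says: "The group with no CRRT is included merely for exploratory analysis of safety aspects and does not affect the power analysis". The registration data set lists both CRRT alone and no CRRT as control comparators.

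**The concern.** Nowhere does the protocol posit that CRRT alone changes bilirubin. Its background sections attribute bilirubin removal to the adsorber. On its own planning assumptions the second test is therefore most naturally read as an expected null. A chain that stops at the first non-significant result will then usually stop there. The third comparison is blocked, although under those assumptions its expected effect equals that of the first.

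The protocol also gives the no-CRRT arm two statuses. The Sample size section treats it as purely exploratory, for safety. The statistical section places two bilirubin comparisons with it inside the confirmatory sequence. Both statements cannot stand, and this holds whatever any simulation shows.

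At stake is whether the third comparison can carry a confirmatory label, and whether a reader can tell which claims about the no-CRRT arm are confirmatory.

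**Working it through.** **Inputs.** From Sample size: 17 per arm, SD 5 mg/dl, 72-h means of 5 (CytoSorb plus CRRT, arm A) and 10 (CRRT, arm B), two-sided 5% t-test, no missing values. Assumed: the no-CRRT arm (C) has a mean of 10 mg/dl, inferred from the planning statement on control patients and the arm's control label. The range is shown in step 3.

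**1. The plan's own figure.** The noncentrality is 5 / (5 × √(2/17)) = 2.92 with 32 degrees of freedom. Exact power is 80.7% at 17 per group and 78.1% at 16, so the stated 17 per group for 80% power reproduces.

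**2. The chain with means 5/10/10.** If B and C have equal means, P(step 3 confirmed) ≤ P(step 2 rejects) ≤ 5% for any valid 5% test, whatever the sample size or baseline adjustment. The actual figure is lower because the tests share arms. Simulation (800,000 trials, pairwise t-tests) gives:

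- A versus B significant: 80.7%
- B versus C significant, taken alone: 5.0%
- A versus B and B versus C both significant (step 3 reached): 3.5%
- all three significant (step 3 confirmed): 2.1%
- A versus B and A versus C both significant (step 3 confirmed without the gate): 69.7%

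With the planned baseline-adjusted regression (HC3 robust errors, 40,000 trials each), step 3 is confirmed in 1.5%, 1.9%, 2.5%, 3.3% and 4.1% of trials at assumed baseline to 72-h correlations of 0, 0.3, 0.5, 0.7 and 0.9.

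**3. Sensitivity to the assumed no-CRRT mean** (t-tests, SD 5, 17 per arm):

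| No-CRRT 72-h mean (mg/dl) | Step 3 confirmed, present chain | Step 3 confirmed, no gate |
|---|---|---|
| 8 | 3.5% | 37% |
| 9 | 2.6% | 56% |
| 10 | 2.1% | 70% |
| 11 | 4.6% | 77% |
| 12 | 12.5% | 80% |
| 13 | 27% | 81% |
| 15 | 62% | 81% |

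**4. Does the gate protect the familywise error?** Consider testing A versus B at 5% and, only if that is significant, B versus C and A versus C each at 5%.

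- If A = B is true, any false claim about A = B, B = C or A = C first requires rejecting A = B, which happens at most 5% of the time.
- If A = B is false, B = C and A = C cannot both be true, since together they imply A = B. At most one true null remains, tested at 5%.

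The familywise error is therefore at most 5% in every configuration, provided each pairwise test holds its own level. Simulation agrees: about 5.0% when A = B (with C equal or different), and about 3.5% when only B = C or only A = C holds with the other arm 5 mg/dl away.

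**5. Is anything lost?** Every set of rejections under the present chain also occurs under the parallel version, because the first test is the same and B versus C is tested under the same condition. Its chance stays at 3.5% with means 5/10/10.

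**The case against.** The order has a rationale. Specific objectives names two comparisons, in this sequence: CytoSorb plus CRRT versus CRRT, then CRRT versus no CRRT. The third comparison is not among them. It mixes the two components that the Discussion wants to assess separately. Putting it last is a defensible priority, and this stands. But it does not justify making the third test depend on the second, because the parallel version leaves the named second comparison exactly where it was.

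The null expectation at step 2 is also an inference. The planning statement on controls sits in a two-group calculation that sets the third arm aside, and no 72-h mean for that arm is given. This stands too, and is why a range is shown.

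Finally, if the chain stops, step 3 is still reported, with emphasis on the estimate and its 95% confidence interval. It loses a label, not its result.

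Stronger readings are tempting. A reader might infer that step 3 can never become confirmatory, but at a no-CRRT mean of 15 mg/dl it does so in 62% of trials. A reader might infer that the main result is compromised, but the first comparison is the primary goal and the only powered one, and it is tested first at the full 5%. A reader might also infer, because the Cox model is spelled out only for the two CRRT arms, that survival in the third arm goes unanalysed. The protocol plans Kaplan-Meier estimates for all three arms and hazard-ratio comparisons of survival under Secondary endpoints. Further descriptive hazard ratios are detail for an analysis plan.

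**Conclusion.** The point holds as a minor one. With a no-CRRT mean of 10 mg/dl, SD 5 and 17 per arm, the third comparison is confirmed in about 2% of trials under the present chain (1.5% to 4.1% with the planned regression), against about 70% without the gate. The first figure depends on the inferred mean. It stays below 5% from 8 to 11 mg/dl and climbs above that.

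Two conclusions need no assumption about the means: the gate adds no familywise protection, and the Sample size and statistical sections disagree on whether the no-CRRT arm is exploratory. The primary comparison, its power of roughly 80% and the validity of the current procedure are not in question.

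**What to change.** Choose one of two consistent versions and write it into both sections.

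- **Keep the arm in the confirmatory analysis.** Test CytoSorb plus CRRT versus CRRT at 5%. If significant, test CRRT versus no CRRT and CytoSorb plus CRRT versus no CRRT in parallel, each at 5%, and state that familywise control follows from the logical relation among the three equalities. Amend Sample size so that it no longer calls the arm merely exploratory, while keeping the statement that it is not powered.
- **Treat the arm as exploratory.** Leave Sample size as it is, limit confirmatory testing to CytoSorb plus CRRT versus CRRT, and declare both no-CRRT bilirubin comparisons descriptive, with estimates and 95% confidence intervals.

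Do not simply swap steps 2 and 3. CRRT versus no CRRT, a named objective, would then need all three tests to succeed, and with means 5/10/10 its chance of a confirmatory result would fall from 3.5% to 2.1%.

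Either version costs about a paragraph of wording, made as an amendment before the data are analysed. It needs no additional patients, data or alpha.

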##### Methods for any additional analyses

Demographic and other baseline data (including disease characteristics) will be summarized descriptively by a randomized treatment arm. Numbers of complete and missing data (if any) will be shown. Relative frequencies will be shown as valid % (number of patients divided by the number of patients with non-missing values).

##### Definition of analysis population relating to protocol non-adherence (e.g., as randomized analysis), and any statistical methods to handle missing data (e.g., multiple imputation)

Efficacy analyses will be performed primarily in the full analysis set (FAS) according to the intention-to-treat (ITT) principle. This means that the patients will be analyzed in the treatment arms to which they were randomized, irrespective of whether they refused or discontinued the treatment or whether other protocol violations are revealed. Regarding the primary endpoint, however, cases of death within 72 h will be excluded from the analysis and reported descriptively. No other types of missing data are expected for the primary endpoint.

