
## Introduction

### Background and rationale

#### Systemic inflammation in decompensated liver cirrhosis and acute-on-chronic liver failure (ACLF)

Liver cirrhosis is a major healthcare problem. Among affected patients mortality is high. In Germany, in 2015 more than 13,000 patients died owing to decompensated cirrhosis [2]. The clinical course of cirrhosis can be separated in compensated and decompensated cirrhosis. Patients with compensated cirrhosis are largely asymptomatic and the development of decompensating events is a major hallmark in the course of the disease as median survival decreases from 12 years to less than 2 years [3]**.** The most important decompensating events are the development of variceal bleeding, ascites, hepatic encephalopathy, and bacterial infections [4]. Previously, liver cirrhosis has been described as a systemic disease affecting almost any other organ system [4, 5]. The development of extrahepatic organ complications in decompensated cirrhosis has been identified as a major prognostic milestone and has been described as acute-on-chronic liver failure (ACLF) [6]. ACLF is understood as a dynamic process and may evolve within days leading to multi-organ failure with renal failure being the most common organ involvement (56%), followed by liver and coagulation failure (44% and 28%, respectively) [6, 7]. ACLF is associated with a high 28-day mortality ranging from 22% to 77% in patients with multi-organ failure [6].

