##### Blood samples

Blood samples will be collected on the same way as blood samples in the clinical routine in our hospital. The samples will be analyzed in the hospital’s central laboratory. Since only parameters will be assessed that are available in clinical routine, no study-specific procedures need to be put in place. Table 3 lists the parameters that will be assessed.

**Table 3 Tab3:** Laboratory parameters assessed at different time points during the study

	0 h	72 h	7 days*
Leukocytes [thous./μl]	x	x	x
Thrombocytes [thous./μl]	x	x	x
Red cell distribution with [%]	x	x	x
Hemoglobin [g/dl]	x	x	x
Hematocrit [%]	x	x	x
Lymphocytes [thous./μl]	x	x	x
Neutrophils [thous./μl]	x	x	x
Monocytes [thous./μl]	x	x	x
INR	x	x	x
PTT [sec.]	x	x	x
D-dimers [mg/l]	x	x	x
Fibrinogen [mg/dl]	x	x	x
Ferritin [ng/ml]	x	x	x
Urea [mg/dl]	x	x	x
Creatinine [mg/dl]	x	x	x
Uric acid [mg/dl]	x	x	x
LDH [U/l]	x	x	x
CK [U/l]	x	x	x
CK-MB [U/l]	x	x	x
Myoglobin [U/l]	x	x	x
Troponin T [ng/ml]	x	x	x
ProBNP [pg/ml]	x	x	x
AST [U/l]	x	x	x
ALT [U/l]	x	x	x
AP [U/l]	x	x	x
g-GT [U/l]	x	x	x
Bilirubin [mg/dl]	x	x	x
Bilirubin direct [mg/dl]	x	x	x
Bile acids [μmol/L]	x	x	x
CRP [mg/l]	x	x	x
PCT [ng/ml]	x	x	x
Protein [g/dl]	x	x	x
Albumin [g/dl]	x	x	x
IL-6 [pg/ml]	x	x	x
TNF-α	x	x	x
Triglycerides [mg/dl]	x	x	x
Cholesterine [mg/dl]	x	x	x
LDL-cholesterine [mg/dl]	x	x	x
HDL-cholesterine [mg/dl]	x	x	x
IgG [mg/dl]	x	x	x

*Parameters after 7 days will only be collected, if they are available within clinical routine. No additional blood samples will be taken

In all patients with CRRT, point-of-care blood gas analysis testing will be performed at least every 4–6 h as part of clinical routine assessments (available parameters: pH, pCO2 [mmHg], pO2 [mmHg], sO2 [%], SBC [mmol/l], Hb [g/dl], Na [mmol/l], K [mmol/l], Ca [mmol/l], Cl [mmol/l], lactate [mmol/l], glucose [mmol/l], bilirubin [mmol/l]). The results from these analyses, including serum bilirubin concentrations, will be available from the patient files and retrieved from the patient records for assessment in this trial. In the no CRRT group, these parameters will most likely not be available for all patients, since not all will require an arterial vascular access and repeated point-of-care blood gas analysis testing.

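### The confirmatory bilirubin analysis is declared intention-to-treat but drops deaths before 72 h, and the sample size assumes that no such deaths occur

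*Protocol article*

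**What the plan says.** The protocol article's section on the definition of the analysis population puts efficacy analyses in the full analysis set under the intention-to-treat principle, with patients analysed as randomised. It then makes an exception: "Regarding the primary endpoint, however, cases of death within 72 h will be excluded from the analysis and reported descriptively". No other missing data are expected for this endpoint.

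The Sample size section plans for the same position: "No missing values up to 72 h are expected". Its contingency reads "In the unexpected event that patients die within the study before reaching the 72-h end point, we will describe an appropriate expansion of enrolment", to be set out in a protocol amendment. Neither the size nor the trigger of that expansion is given.

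The introduction says of the disease: "ACLF is associated with a high 28-day mortality ranging from 22% to 77% in patients with multi-organ failure".

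Under Statistical methods, the primary test is a linear regression of 72-h bilirubin on treatment and baseline bilirubin with robust standard errors. It is the only place where confirmatory testing is allowed. Under Secondary endpoints, death within 30 days is handled differently: ventilator-, vasopressor- and dialysis-free days are set to 0 for patients who die, and arms are compared by the C-index.

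**The concern.** Two statements in the plan conflict with other parts of it.

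First, an analysis that removes patients because they died after randomisation is not intention-to-treat. Early death may depend on the allocated treatment and on how bilirubin is developing. If it depends on both, the arms left for analysis are no longer comparable by randomisation. This possibility is not remote here. The section on risks of the CytoSorb device cites a small randomised trial (34 COVID-19 patients on ECMO) in which adsorption was associated with higher mortality, and the early-termination rules refer to it.

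Second, treating death before 72 h as unexpected sits badly with the mortality that the protocol itself cites. All eligible patients have ACLF with stage 3 kidney injury and bilirubin of at least 5 mg/dl, and the exclusion for a planned stop of treatment covers only the next 24 h.

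At stake are what the one confirmatory result means and whether the stated power applies to the number of patients who will be analysed. The contingency adds a further problem. The trial is open-label without a data monitoring committee, and the investigators and the statistician discuss accumating results after every fifth patient. An expansion whose rule is not fixed in advance would thus be decided by people who can see arm-level data.

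**Working it through.** **Inputs from the Sample size section.** The test is a two-group t-test, and "with a two-sided significance level of 5%, a sample size of 17 patients in each group yields a power of 80" per cent, if "mean serum bilirubin levels after 72 h differ by 5 mg/dl, given a standard deviation of 5 mg/dl in both groups". Only the two CRRT arms count (17 + 17 = 34): "The group with no CRRT is included merely for exploratory analysis of safety aspects and does not affect the power analysis". The allowance for loss is zero. The introduction gives 28-day mortality of 22% to 77%. No 72-h mortality is given anywhere.

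**1. The plan's own figure.** The noncentrality is 5 / (5·√(2/17)) = 2.915 with 32 degrees of freedom. Power is 80.7%, so the stated 80% reproduces. At 16 per arm it is 78.1%, so 17 is the smallest number that reaches 80%.

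**2. Early deaths implied by the cited mortality.** Assume a constant hazard, so that p = 1 − (1 − m)^(3/28), where m is 28-day mortality.

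| 28-day mortality m | p by 72 h | Expected deaths, 34·p | Chance of none, (1 − p)^34 |
|---|---|---|---|
| 22% | 2.6% | 0.9 | 40% |
| 77% | 14.6% | 5.0 | 0.5% |

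**3. Power if deaths are excluded and not replaced (unadjusted t-test).** With equal survivor numbers per arm: 16 gives 78.1%, 15 gives 75.3%, 14 gives 72.1%. Averaged over binomial survivor numbers, by assumed early-death rate: 3% gives 79.4%, 5% gives 78.4%, 10% gives 75.9%, 15% gives 73.2%.

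**4. Effect of the planned baseline adjustment.** The residual SD is 5·√(1 − ρ²), where ρ is the correlation of baseline with 72-h bilirubin. The protocol does not state ρ, so these values are assumptions.

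| ρ | Residual SD | 17 per arm | 15 per arm | 13 per arm |
|---|---|---|---|---|
| 0 | 5.00 | 80.7% | 75.3% | 68.7% |
| 0.3 | 4.77 | 84.2% | 79.1% | 72.7% |
| 0.5 | 4.33 | 90.4% | 86.3% | 80.6% |

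**5. Size and direction of the survivor bias.** Suppose treatment has no effect on bilirubin (mean 10, SD 5), and death is more likely at higher bilirubin (log-odds slope 0.2 per mg/dl, an assumption).
- With 15% early deaths under CytoSorb and 5% under control, the difference in survivor means is −0.43 mg/dl, which looks like benefit.
- With the two rates exchanged it is +0.43 mg/dl.
- With 10% in both arms it is 0.

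A simulation of the planned regression used a steeper slope (log-odds 1.1 per SD), 14.6% against 2.6% early mortality, and ρ from 0 to 0.7. It gave a bias of about −0.3 to −0.5 mg/dl, with type I error still close to 5%. A stress case of 25% against 5%, beyond the range in step 2, gave at most about −0.9 mg/dl and type I error of about 5% to 7%.

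**The case against.** The case for leaving the plan as it stands has real weight.

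- **Power.** A reader might infer that the stated 80% is wrong or will not be delivered. The documents do not support that. The figure reproduces, the Sample size section commits to expanding enrolment if early deaths occur, and the primary model adjusts for baseline, which the protocol expects to raise power. With ρ = 0.5, 13 per arm would still give 80.6%. The shortfall is conditional on no replacement and little gain from adjustment.
- **Bias.** A reader might infer that the randomised comparison is invalid or that a false positive is likely. Step 5 does not show this. Against a planned difference of 5 mg/dl, the bias is a few tenths of a mg/dl even under a strong assumed mortality imbalance, and its sign depends on which arm has more deaths.
- **Early CRRT.** A reader might infer that harm from early CRRT would distort the main result. Both arms of the powered comparison start CRRT early, so that could matter only for comparisons with the no-CRRT arm.
- **Transparency.** Early deaths are not hidden. The exclusion is stated openly, the deaths are reported descriptively, and they enter the survival analysis. Sensitivity analyses may also be left to an analysis plan that is not shown.

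What remains is not a missing detail. The protocol fixes a rule for its sole confirmatory test that departs from the principle it declares, and a zero-loss assumption that its own mortality figures make implausible. Extra enrolment restores numbers but does not undo selection on survival.

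**Conclusion.** The point holds as an inconsistency in a stated rule, with a modest expected effect. The confirmatory analysis is a survivors-only comparison and should not be described as intention-to-treat. The bias can favour either arm. Under the assumptions tried it is small against 5 mg/dl, so it matters mainly for a borderline result and for what the result means.

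The expectation of no loss before 72 h conflicts with the cited 28-day mortality. About 1 to 5 early deaths among 34 patients is the range at constant hazard, and at the upper end a trial without any is very unlikely (0.5%). Mortality concentrated early or late would move these figures up or down.

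The 80% power is correct for 17 evaluable patients per arm. At 3% to 15% early death without replacement it becomes about 73% to 79% for the unadjusted t-test, and higher with baseline adjustment by an amount that depends on the unstated correlation.

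**What to change.** 1. **Label and companion analysis.** Describe the death-excluded regression as an analysis of patients alive at 72 h, not as intention-to-treat. Pre-specify beside it an analysis of all randomised patients that ranks death before 72 h worse than any bilirubin value. The C-index and death-as-worst approach already used for the free-day endpoints would serve. Interpret any superiority conclusion in light of this analysis. An analysis using the last bilirubin before death can be a further sensitivity analysis for the two CRRT arms, where "point-of-care blood gas analysis testing will be performed at least every 4–6 h as part of clinical routine assessments". It does not suit the no-CRRT arm, because the Blood samples section says such values will probably not exist for all of those patients.
2. **Loss assumption.** Replace the zero-loss statement with an assumed early-death rate and state the power conditional on it: about 73% to 79% for the unadjusted t-test at 15% to 3% early death without replacement, higher with baseline adjustment. If 17 evaluable patients per arm are to be kept, 17/(1 − 0.10) = 18.9 means 19 per arm at 10%, and 17/(1 − 0.15) = 20 per arm at 15%.
3. **Expansion rule.** State now that any expansion of enrolment depends only on the pooled number of early deaths and not on arm-level bilirubin. Say also that it restores numbers without removing the survivor bias.

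The cost is wording, one or two extra analyses and a slightly less favourable stated power. The worst-rank analysis also has less power. Under the planned effect with equal early mortality in both arms, simulation gives about 79% with no deaths, 67% at 5%, 56% at 10% and 48% at 15%. It should therefore inform the interpretation and not be a second test that must reach significance.
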